### Interventions

2.3

After discharge, all enrolled patients will be advised to consume their diet as tolerated, with a focus on eating 5–6 meals per day to avoid gastrointestinal overload. Moreover, patients in PERT group will oral Pancreatin Enteric-coated Capsules (produce by Abbott laboratories GmbH, H20171150), each capsule contains 150 mg pancrelipase microgranules (lipase 10,000 U. Ph. Eur., amylase 8,000 U. Ph. Eur., protease 600 U. Ph. Eur.) which was derived from pig pancreas. The Capsules are commercially available and issued by the project team. According to guidelines (Dominguez-Muñoz et al., 2025; Smith et al., 2016; Gheorghe et al., 2015), we design that the patients after discharge take three capsules (30,000 U) with food three times a day for 1 month in this study. The first participant was enrolled on 6 June 2025.

### Outcomes

2.4

The primary outcome of the trial is the incidence of gastrointestinal symptoms at 1 month postoperatively in gastric cancer patients. Seven gastrointestinal symptoms (pain, dysphagia, nausea, vomiting, abdominal distension, constipation and diarrhea) are assessed using the MD Anderson Symptom Inventory Gastrointestinal Cancer Module (MDASI-GI) (Wang et al., 2010). We use a 0–10 numerical rating scale (NRS) to assess the severity of symptoms, with 0 being “not present” and 10 being “as bad as you can imagine.” Secondary outcomes include nutritional status and patient compliance. Nutritional status was assessed using the Nutritional Risk Screening 2002 (NRS 2002), Patients were classified as high risk when NRS score was 3 and low risk when NRS score was <3. In addition, hematological markers including lymphocyte count, hemoglobin, serum albumin, and prealbumin also reflected nutritional status, the lower the value, the more severity of malnutrition. Medication adherence in the PERT group is documented through Medication Record Cards.

### Follow-up

2.5

The MDASI-GI and NRS2002 were assessed by patients via Wenjuanxing App. Assessment of MDASI-GI, NRS2002, and blood samples for lymphocyte count, hemoglobin, serum albumin, and prealbumin were collected at baseline before surgery. Follow-up begins postoperatively and continues for 1 month after discharge. Assessment of MDASI-GI occurs at postoperative day 2 (POD 2), postoperative day 7 (POD 7), and twice weekly following discharge. NRS2002 and blood samples are collected once every 2 weeks after discharge (Figure 2). Patients’ self-reported Medication adherence will be recorded. If a patient decides to withdraw, the follow-up will be stopped.

**FIGURE 2 F2:**
[figure not shown]
Study schedule. POD, postoperative day; PDW, postdischarge week.

### Sample size

2.6

The primary outcome of this study is the incidence of gastrointestinal symptoms 1 month after surgery. According to our previous research (Xu et al., 2022), the incidence of gastrointestinal symptoms 1 month after gastric cancer surgery is 50%. The incidence of gastrointestinal symptoms in PERT group is expected to be 30%. The required number of patients has been calculated by PASS V.15.0 software and based on a two-sided significance level of 5%, and a statistical power of 80%. Thus, 204 patients need to be recruited into this study (102 patients in each group) in view of a 10% dropout rate.

### Statistical analysis

2.7

Continuous variables will be presented as mean ± standard deviation (SD), and categorical variables will be presented as numbers (percentages). The χ^2^ or Fisher’s exact test apply to present the difference of the primary outcome. The t-test is used to demonstrate the statistical difference of the continuous variables such as MDASI-GI score, NRS2002 score and hematological indicators. In addition, the logistic regression (age, sex, nutrition status, style of gastrectomy, PERT will be included as influencing factors) will be used to identify the risk factors affecting the incidence of gastrointestinal symptoms. All randomly assigned patients who receive at least one dose of the study medication will be included in the full analysis set (FAS) according to the intention-to-treat (ITT) principle, and at least one evaluable efficacy outcome is used for the analysis of all efficacy outcomes and baseline characteristics of patients. Patients with study drug adherence of <50% will not be included in the analysis. Statistical significance was defined as a p-value less than 0.05.

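### Continuous outcomes are compared by an unadjusted t-test although a pre-surgery value of each is collected, giving up precision that costs nothing to keep

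*Protocol article*

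**What the plan says.** Section 2.7 (Statistical analysis) gives one method for all continuous outcomes: "The t-test is used to demonstrate the statistical difference of the continuous variables such as MDASI-GI score, NRS2002 score and hematological indicators". It mentions no baseline adjustment and no visit for this test. The threshold is general: "Statistical significance was defined as a p-value less than 0.05". The only model with covariates is a logistic regression for the binary symptom outcome, which "will be used to identify the risk factors affecting the incidence of gastrointestinal symptoms".

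Section 2.5 (Follow-up) sets out the data available:

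- Baseline: "Assessment of MDASI-GI, NRS2002, and blood samples for lymphocyte count, hemoglobin, serum albumin, and prealbumin were collected at baseline before surgery".
- Symptom score: "Assessment of MDASI-GI occurs at postoperative day 2 (POD 2), postoperative day 7 (POD 7), and twice weekly following discharge".
- Nutrition: "NRS2002 and blood samples are collected once every 2 weeks after discharge".
- Duration: "Follow-up begins postoperatively and continues for 1 month after discharge".

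Section 2.4 (Outcomes) lists nutritional status and compliance as the secondary outcomes. MDASI-GI appears there as the instrument behind the binary primary outcome, so its continuous score is a supporting measure.

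**The concern.** A two-sample t-test on a follow-up value treats all between-patient variation as noise. Part of that variation was already present before surgery and has been measured. Analysis of covariance removes the part that baseline predicts, still estimates the same treatment difference, and needs nothing that is not already being collected.

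The continuous nutritional outcomes have most to gain. The 204 patients were sized on the binary primary outcome alone (section 2.6), so no power was planned for the continuous comparisons.

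A second, smaller matter follows from the same sentence. The outcomes are measured repeatedly but the test is not tied to a visit, which leaves room to choose among visits after the data are seen. This deserves care for a self-reported score in an open-label trial.

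**Working it through.** **1. The plan's own figure.** Section 2.6 gives 50% versus 30%, two-sided 5%, 80% power and 10% dropout. With unpooled variance, n per arm = (1.960 + 0.842)² × (0.5×0.5 + 0.3×0.7) / 0.20² = 90.3, rounded up to 91. Then 91 / 0.9 = 101.1, rounded up to 102 per arm, or 204 in all. The stated figure is reproduced. It rests on the binary outcome, so nothing below changes it.

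**2. Reference case for a continuous outcome.** Evaluable patients per arm: 102 × 0.9 = 91.8, taken as 92. A t-test at one visit has 80% power for a difference of 2.802 × √(2/92) = 0.413 SD.

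**3. Effect of baseline adjustment.** With correlation ρ between the pre-surgery and follow-up values, ANCOVA multiplies the variance by 1 − ρ². Power at 0.413 SD becomes Φ(2.802/√(1 − ρ²) − 1.960). The number per arm that a t-test would need for the same precision is 92/(1 − ρ²). The article gives no correlation, so ρ is an assumption.

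| ρ | Variance factor | Power at 0.413 SD | Equivalent t-test n per arm |
|---|---|---|---|
| 0.2 | 0.96 | 81.6% | 96 |
| 0.3 | 0.91 | 83.6% | 102 |
| 0.4 | 0.84 | 86.4% | 110 |
| 0.5 | 0.75 | 89.9% | 123 |
| 0.6 | 0.64 | 93.8% | 144 |

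**4. If the t-test were run on change from baseline.** The variance factor would be 2(1 − ρ): 1.6 at ρ = 0.2, 1.0 at 0.5 and 0.8 at 0.6. ANCOVA gives 0.96, 0.75 and 0.64, so it is more precise under either reading.

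**5. Why one visit should be named.** Taking 1 month as about four weeks, twice-weekly assessment gives about 8 post-discharge MDASI-GI values, and two-weekly collection gives about 2 values of NRS2002 and each blood marker. If every visit were tested at 5% with no true effect, the chance of at least one p < 0.05 is:

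- 8 visits: 1 − 0.95⁸ = 33.7% if independent; by simulation with equal between-visit correlation 0.3, 0.5 and 0.7, it is 30.1%, 24.9% and 19.1%.
- 2 visits: 1 − 0.95² = 9.8% if independent; at the same correlations, 9.5%, 9.0% and 8.4%.

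These figures are conditional on visit-by-visit testing. POD 2 is left out, and POD 7 with it, because study treatment starts only after discharge (section 2.3).

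**The case against.** The strongest reply is that nothing here is an error. Under randomisation a t-test at a fixed visit is unbiased and holds its type I error, and chance baseline imbalance is already reflected in its standard error. The outcomes concerned are not primary. This stands, and it limits the point to a gain in precision. A reader might infer that the t-test gives biased or invalid results; the documents do not support that.

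A reader might also infer that the trial will test every visit at 5%. Section 2.7 does not say so. The choice of visit, any multiplicity rule and the handling of missing values are details that a full protocol or analysis plan may settle. Nor can the 19% to 30% be attached to the declared secondary outcomes: it concerns only the MDASI-GI score, which section 2.4 does not list as a secondary outcome. For nutritional measures with about two visits the figure is 8.4% to 9.5% per outcome.

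The size of the gain is also open to challenge. The baseline precedes a gastrectomy, which the Discussion itself says changes anatomy and physiology markedly, so a weak correlation is plausible, particularly for symptoms. At ρ = 0.2 the benefit is slight. That is why the range starts there.

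Finally, a large gain from the repeated measurements might be expected. It would arise from averaging a constant effect over visits. With complete data, a single-visit contrast from a mixed model has essentially the precision of ANCOVA, and the repeats help mainly when values are missing.

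None of this is a reason to keep the unadjusted test. The article names that test, so it is a stated choice and not a detail left for later.

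**Conclusion.** The point holds as a low-cost improvement to a stated method. The unadjusted t-test is valid but discards a baseline the trial collects for every continuous outcome. With a correlation of 0.2 to 0.6, adjustment reduces variance by 4% to 36% and moves 80% power to about 82% to 94%. That range rests on an assumed correlation, a normal approximation and 92 evaluable patients per arm; at the low end the gain is small. The primary analysis and the sample size are not affected. Naming one visit per outcome is a sensible part of the same change, but the article does not show that multiple visits will be tested.

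**What to change.** In section 2.7, and in any analysis plan that follows it, replace the t-test for continuous outcomes with ANCOVA on the value at one named visit per outcome. The covariates are treatment arm, the pre-surgery value of the same measure and gastrectomy type. Type of gastrectomy is already a factor in the planned logistic regression and is settled before the first dose.

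A mixed model for repeated measures with the same covariates is an acceptable alternative, useful if visits are missed. For MDASI-GI an unstructured covariance over 8 visits has 8 × 9 / 2 = 36 parameters, so a simpler fallback structure should be specified in advance.

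For the MDASI-GI score, use the 1-month postoperative time point of the primary outcome and report the other visits descriptively. A visit defined as four weeks after discharge would introduce a second time definition. For NRS2002 and the blood markers, the sponsor should name one of the two-weekly post-discharge visits.

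The cost is analysis wording and minor programming. No new data, visits or patients are needed. Enrolment began in June 2025, so the change should be recorded before any outcome is compared by arm.

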### Trial design

2.1

The PERT-GC01 trial is a multicenter randomized controlled trial (ChiCTR Identifier: ChiCTR2500102557), gastric cancer following radical gastrectomy will be randomized in a 1:1 ratio to the PERT group or the control group. A randomization schedule will be generated by computer to assign subjects to the treatment sequences. A total of 204 patients will be recruited from seven large-scale gastrointestinal medical centers in China which include Sichuan Cancer Hospital, Chengdu First People’s Hospital, Chengdu Second People’s Hospital, Chengdu Third People’s Hospital, Mianyang People’s Hospital, Mianyang Third People’s Hospital and Langzhong People’s Hospital. This study was approved by the Ethics Committee for Medical Research and New Medical Technology of Sichuan Cancer Hospital (SCCHEC-02-2025-008). The study design is summarized in Figure 1.

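### The primary comparison is valid but ignores the pre-surgery MDASI-GI score already collected, and the additional logistic model lists nutrition status without a time point

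*Protocol article*

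**What the plan says.** Statistical analysis (2.7) assigns the primary outcome, gastrointestinal symptoms at 1 month, to a chi-square or Fisher's exact test with no covariates. As a further analysis aimed at finding risk factors, it describes "the logistic regression (age, sex, nutrition status, style of gastrectomy, PERT will be included as influencing factors". The list is explicit. It contains no MDASI-GI score and no centre, and it does not say when nutrition status is measured.

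Three other sections bear on this:

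- Outcomes (2.4): "Secondary outcomes include nutritional status and patient compliance".
- Follow-up (2.5): MDASI-GI, NRS2002 and the blood markers are all taken at a baseline before surgery. During the treatment month, "NRS2002 and blood samples are collected once every 2 weeks after discharge".
- Trial design (2.1): "A total of 204 patients will be recruited from seven large-scale gastrointestinal medical centers in China". A computer-generated schedule is described, and stratification is not mentioned.

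**The concern.** There are two separate issues.

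The first is efficiency. MDASI-GI is the instrument that defines the primary outcome, and each patient completes it before surgery. A baseline reading on the outcome's own scale is a natural covariate and costs nothing further to collect. The plan uses it neither in the primary test nor in the logistic model, so any precision it could add is lost.

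The second is an ambiguous covariate. Nutrition status could mean the pre-surgery value or one taken after discharge while PERT is being given. The protocol treats nutrition as something PERT may improve: it is a secondary outcome, and the Discussion cites an earlier randomised trial of PERT in which it improved. A post-discharge value placed beside PERT would hold constant part of what the drug may do. The text allows both readings, and they give different PERT odds ratios. Because PERT is one of the listed factors, the model will produce such an odds ratio, and readers will set it beside the primary result.

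**Working it through.** **1. The plan's own sample size.** Inputs from Sample size (2.6): 50% in control, 30% under PERT, two-sided 5%, 80% power, 10% dropout. Allocation is 1:1 (Trial design). With unpooled variance:

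n per arm = (1.960 + 0.842)² × (0.50×0.50 + 0.30×0.70) / 0.20² = 7.85 × 0.46 / 0.04 = 90.3, so 91.

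Allowing for dropout, 91 / 0.90 = 101.1, so 102 per arm and **204** in total, which is the stated figure. The pooled-variance formula gives 93 per arm and 208 in total. With 102 × 0.9 ≈ 92 evaluable per arm, the unadjusted test has 79.6% power (pooled formula). The planned test therefore delivers the planned power.

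**2. What the baseline score could add.** This was simulated with 92 per arm and marginal rates held at 50% and 30%. A standard normal baseline score had latent correlation ρ with the outcome. The unadjusted test was compared with the Wald test for PERT in a logistic model on arm and score, using 4000 runs per row. The values of ρ are assumptions.

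| ρ | Unadjusted power | Adjusted power | Gain (points) |
|---|---|---|---|
| 0 | 79.5% | 79.5% | 0 |
| 0.2 | 79.9% | 81.1% | 1.2 |
| 0.3 | 79.3% | 81.6% | 2.3 |
| 0.5 | 79.5% | 85.7% | 6.2 |
| 0.7 | 79.0% | 91.5% | 12.5 |

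The simulation error of each power figure is about √(0.8×0.2/4000) = 0.6 points. A separate simulation using the likelihood-ratio test gave 82% at ρ = 0.3 and 87% at ρ = 0.5, with type I error of 5-6%.

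**3. What the timing of nutrition status does.** The odds ratio implied by the planned rates is (0.30/0.70) / (0.50/0.50) = 0.43. Assumptions: half of control patients are at nutritional risk, risk carries an odds ratio of 2 or 4 for symptoms, and PERT lowers the proportion at risk by 0 points (a pre-surgery value), 10 points or 20 points (a post-discharge value). The total effect stays at 50% versus 30%. Each row has 3000 runs.

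| Nutrition value | OR of risk for symptoms | PERT OR given nutrition | Power for PERT term |
|---|---|---|---|
| Pre-surgery | 2 | 0.42 | 81% |
| Pre-surgery | 4 | 0.39 | 85% |
| Post-discharge, 10 points lower | 2 | 0.45 | 72% |
| Post-discharge, 10 points lower | 4 | 0.45 | 68% |
| Post-discharge, 20 points lower | 2 | 0.48 | 63% |
| Post-discharge, 20 points lower | 4 | 0.53 | 50% |

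The last row can be checked by hand.

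- Control: the odds of symptoms are 0.5 without risk and 2 with risk, so the average is 0.5×(1/3) + 0.5×(2/3) = 0.50.
- PERT: odds of 0.2635 without risk and 1.054 with risk give 0.7×0.2085 + 0.3×0.513 = 0.30.
- The conditional odds ratio is 0.2635 / 0.5 = 0.53.

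In the pre-surgery rows the odds ratio lies slightly further from 1 than 0.43. That is the usual difference between conditional and marginal odds ratios and does not mean the effect is larger. It is also why a standardised risk difference is the better summary.

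**4. Room for covariates.** Expected events are 92×0.5 + 92×0.3 = 73.6, about 74.

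**The case against.** The strongest reply is that nothing here is wrong. An unadjusted test is valid under randomisation, the sample size was built for it, and an adjusted analysis is only a possible improvement. The size of that improvement rests on a correlation the article does not give. A score taken before gastrectomy may say little about symptoms a month after it, since the Discussion itself stresses how much the operation changes anatomy and physiology. All of this stands, and it limits the first issue to a recommendation.

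Four stronger readings are tempting, and the document does not support them.

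- **Nutrition status is a post-treatment covariate.** The text does not say so. A pre-surgery value exists, and the other patient covariates are settled before the drug starts, so the harmless reading is at least as natural. The defect is that the time point is left open within an explicit list.
- **The primary result is biased or underpowered.** The logistic model is an additional analysis and cannot alter the chi-square result. Power falls short only in comparison with an adjusted analysis.
- **Centre must be in the model.** No stratification by centre is described, so leaving it out ignores no stated design factor.
- **An in-hospital score must be in the model.** The article does not date randomisation relative to postoperative days 2 and 7, so it is unclear whether such a score is a pre-randomisation value.

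A large model would also be unwise. Two symptom scores, NRS2002, gastrectomy type, arm and six centre terms come to 11 coefficients, or 74 / 11 = 6.7 events each, and no such model was simulated.

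**Conclusion.** The point holds as a moderate improvement plus one necessary clarification.

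The unadjusted primary test is sound and reproduces the 204 patients. Not using the pre-surgery MDASI-GI score forgoes about 1 to 6 points of power for assumed correlations of 0.2 to 0.5, and practically none if the correlation is near zero.

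The open time point matters more for interpretation. If a post-discharge nutrition value were used, the PERT odds ratio in the additional model would move from 0.43 to 0.45-0.53, and power for that term would fall to 50-72%. These figures assume that PERT lowers nutritional risk by 10 to 20 points, that risk carries an odds ratio of 2 to 4 for symptoms, and that nutrition and symptoms share no unmeasured cause. With a pre-surgery value, nothing is adjusted away.

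**What to change.** Before anyone looks at outcome data by arm:

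1. Pre-specify a logistic analysis of the primary outcome on arm, pre-surgery MDASI-GI gastrointestinal score, gastrectomy type and pre-surgery NRS2002. Report a standardised risk difference with 95% CI.
2. Keep the unadjusted chi-square test alongside it, and state in advance which of the two carries the primary conclusion. The power gain reaches the primary conclusion only if the adjusted analysis carries it.
3. In the risk-factor model, replace nutrition status with *pre-surgery nutrition status*. State that no post-randomisation covariate enters any model containing PERT.

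No new data are needed. The model has four coefficients besides the intercept if gastrectomy type has two categories, so about 74 / 4 = 18 expected events per coefficient. The simulated model carried one baseline score only, so the power figures are a guide to this slightly larger model. Interventions (2.3) dates the first enrolment to 6 June 2025, so the change needs a dated, documented amendment. In an open-label trial, that amendment should record that outcomes by arm had not been seen.

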# Efficacy of pancreatic enzyme replacement therapy (PERT) in the treatment of gastrointestinal symptoms after gastric cancer surgery: study protocol for a multicenter randomized controlled open-label trial

**DOI:** 10.3389/fphar.2026.1779727

**Published:** 2026-03-11

**Keywords:** gastric cancer, gastrointestinal symptoms, pancreatic enzyme replacement therapy, pancreatic exocrine insufficiency, surgery

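### The full analysis set is conditioned on taking study medication, which only the PERT arm is given, so the population labelled intention-to-treat can exclude patients from one arm only

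*Protocol article*

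**What the plan says.** Section 2.7 (Statistical analysis) of the protocol article sets the entry rule: "All randomly assigned patients who receive at least one dose of the study medication will be included in the full analysis set (FAS". The same sentence says that the set is formed "according to the intention-to-treat (ITT) principle" and uses it for efficacy outcomes and baseline characteristics. The section then adds: "Patients with study drug adherence of <50% will not be included in the analysis".

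Other sections show who can meet or fail these rules:

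- Section 2.3 (Interventions), treatment common to both arms: "all enrolled patients will be advised to consume their diet as tolerated".
- Section 2.3, the capsules: "Moreover, patients in PERT group will oral Pancreatin Enteric-coated Capsules". No placebo or other control drug is described.
- Section 2.4 (Outcomes): "Medication adherence in the PERT group is documented through Medication Record Cards". No adherence record is described for controls.
- The title calls the article a "study protocol for a multicenter randomized controlled open-label trial".
- Table 1, exclusion criterion 8, lists stopping the experimental medication for more than 2 weeks.

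**The concern.** Entry to the primary population depends on something that happens after randomisation and is described for one arm only. Taken at its word, the rule leaves the control arm empty. Taken as it would be applied, controls stay in whatever they do, while PERT patients must first take a capsule and then reach 50% adherence.

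Patients know their arm, the capsules start after discharge, and the primary outcome is self-reported symptoms. Whether a patient starts or continues the capsules can therefore plausibly depend on how that patient feels. Removing such patients from one arm breaks the comparability that randomisation provides, and the intention-to-treat label hides it.

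**Working it through.** **1. The plan's own sample size.** Inputs from section 2.6: 50% against 30%, two-sided 5%, power 80%, 10% dropout. With unpooled variance:

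n = (0.50×0.50 + 0.30×0.70) × (1.960 + 0.842)² / 0.20² = 0.46 × 7.85 / 0.04 ≈ 90.3, so 91 per arm.

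91 / 0.90 = 101.1, so 102 per arm and 204 in total. The stated figure is reproduced. The fault lies in the set definition, not in N.

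**2. Who each rule can remove.**

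| Rule | PERT | Control |
|---|---|---|
| At least one dose, literal reading | never-starters removed | all 102 removed |
| At least one dose, as intended | never-starters removed | nobody |
| Adherence below 50% | never-starters and low adherers removed | nobody |
| Criterion 8, if applied after randomisation | those who stop for more than 2 weeks removed | nobody |

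Zero doses means 0% adherence, and 0% is below 50%. Never-starters are therefore a subset of the patients removed by the adherence sentence. While that sentence stands, the one-dose condition adds no bias of its own on the intended reading. The quantity that matters is the total share f of the PERT arm removed by either rule.

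**3. Size of the bias under no drug effect.** Let the true rate be 50% in both arms (the plan's control rate), f the share of PERT excluded and q the symptom rate among those excluded. Both f and q are assumptions; the documents give neither. The rate among the PERT patients who remain is

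p = (0.50 − f×q) / (1 − f).

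Examples:

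- f = 5%, q = 70%: (0.50 − 0.035)/0.95 = 48.9%
- f = 10%, q = 90%: (0.50 − 0.09)/0.90 = 45.6%
- f = 10%, q = 30%: (0.50 − 0.03)/0.90 = 52.2%

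| f | q = 30% | q = 50% | q = 70% | q = 90% |
|---|---|---|---|---|
| 5% | +1.1 | 0 | −1.1 | −2.1 |
| 10% | +2.2 | 0 | −2.2 | −4.4 |

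Entries are the shift in the PERT rate in percentage points; a minus favours PERT. For a two-sided test at nominal 5% with 102 controls and 102×(1 − f) PERT patients (normal approximation), the type I error for q = 70–90% is 5.3–6.0% at f = 5% and 6.1–9.5% at f = 10%.

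**4. Power with all randomised patients kept.** At 50% against 30%, power is about 83.5% with 102 per arm and about 79.6% with 92 per arm, in line with the planned 80%.

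**The case against.** **The empty control arm is only a wording slip.** This stands. Section 2.6 plans 102 patients per group and section 2.7 specifies a between-arm test, so controls are plainly meant to be analysed. A reader might infer that the trial cannot make its comparison; the documents do not support that. The text still needs correcting, because no rule for controls is given.

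**The one-dose rule does nothing that the adherence rule does not already do.** This also stands. A reader might add a separate bias for never-starters to that from low adherers. That would count the same patients twice. It also means that deleting the one-dose condition alone would change nothing.

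**The direction is not known.** Correct. Patients who feel well may be the ones who do not bother with capsules. Then q is below 50% and the exclusion works against PERT. A claim that the rule must favour PERT goes beyond the documents.

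**Controls might receive something.** No sentence states outright that they receive no study medication, and Figure 1 is not shown. The inference rests on sections 2.3 and 2.4 and the title, and nothing in the document points the other way.

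**The requirement for an evaluable efficacy outcome.** A reader might add that an early assessment could satisfy it, since "Assessment of MDASI-GI occurs at postoperative day 2 (POD 2), postoperative day 7 (POD 7), and twice weekly following discharge". The clause is garbled, what counts as evaluable is not defined, and the day of discharge is not given. Admitting patients without an on-treatment outcome is also what intention-to-treat requires. This is not a separate fault.

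None of this rescues the definition: a set conditioned on one arm's dosing and adherence is not intention-to-treat.

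**Conclusion.** The definition in section 2.7 is wrong as written and should be corrected. Literally it admits no controls. As intended, it and the adherence sentence together form a single exclusion that can act only on the PERT arm, contrary to the stated principle. That conclusion needs no assumption beyond study medication being given to the PERT arm only.

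The size does depend on assumptions. With 5–10% of PERT excluded and a symptom rate of 70–90% among them, the spurious benefit is about 1.1 to 4.4 points. That is modest against the planned 20-point difference. It is zero if the excluded patients resemble the rest and reversed if they have fewer symptoms. The case for the change rests on the set not being what it is called, not on any one of these figures.

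**What to change.** Replace the definition with: the primary full analysis set is all randomised patients, analysed in the arm assigned, regardless of whether any capsule was taken and regardless of adherence. Remove both the one-dose condition and the exclusion for adherence below 50% from the primary analysis; removing only the first leaves every never-starter out. Keep dose- and adherence-based sets as supplementary analyses, named as such. State that exclusion criterion 8 does not remove randomised patients from the primary set. Enrolment began on 6 June 2025 and the trial is open-label, so the change should be fixed before any comparison by arm.

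Costs:

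- **Dilution.** Section 2.6 expects 30% in the PERT group without restricting it to adherers, so N = 204 is unchanged. If 30% holds only for adherers and 5–10% of the arm gains nothing (an assumption), the arm's rate becomes 0.95×30 + 0.05×50 = 31% to 0.90×30 + 0.10×50 = 32%. The difference then shrinks from 20 points to 19 or 18.
- **Missing outcomes.** Section 2.5 stops follow-up at withdrawal, so some patients in the set will lack a 1-month outcome. Their handling must be specified; the method can be left to the analysis plan.

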### Eligibility criteria

2.2

The inclusion and exclusion criteria for patients were listed in Table 1.

**TABLE 1 T1:** The inclusion and exclusion criteria for this study.

Inclusion criteria	
1	Male or female aged 18–75 years.
2	Histologically confirmed gastric adenocarcinoma and feasible radical resection for gastric cancer.
3	Eastern Cooperative Oncology Group (ECOG) score of 0 or 1.
4	The main organ function is normal.
5	Informed consent form signed.
Exclusion criteria	
1	Other active malignant tumors within 5 years or at the same time.
2	History of pancreatic disease within half a year.
3	Distant metastasis confirmed by imaging or pathological examination.
4	Allergic to any component of the therapy.
5	Human immunodeficiency virus (HIV) infection.
6	Vulnerable groups, including mentally ill, cognitively impaired, critically ill patients, minors, pregnant or lactating women, illiterate, etc.
7	Severe postoperative complications, including anastomotic fistula, intestinal obstruction, abdominal bleeding, severe infection.
8	Stop taking the experimental medication for more than 2 weeks.

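### Excluding patients below 50% drug adherence removes patients from the PERT arm only, contradicts the claimed ITT analysis, and can bias the primary comparison, plausibly towards PERT

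*Protocol article*

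**What the plan says.** Section 2.7 (Statistical analysis) defines the main analysis population in these words: "All randomly assigned patients who receive at least one dose of the study medication will be included in the full analysis set (FAS". It says this is done "according to the intention-to-treat (ITT) principle". The adherence rule follows directly: "Patients with study drug adherence of <50% will not be included in the analysis". The rule is stated for the analysis as a whole. The article names no per-protocol or sensitivity set to which it might belong.

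Three other places show whom the rule can reach:

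- Section 2.3 (Interventions): both arms receive dietary advice, and the drug is given to one arm: "Moreover, patients in PERT group will oral Pancreatin Enteric-coated Capsules".
- Title: "study protocol for a multicenter randomized controlled open-label trial". No placebo is described anywhere.
- Section 2.4 (Outcomes): "Medication adherence in the PERT group is documented through Medication Record Cards". No adherence record is described for controls.

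Table 1 (section 2.2) lists as exclusion criterion 8: "Stop taking the experimental medication for more than 2 weeks". This too can happen only after treatment has started, and only in the PERT arm.

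**The concern.** Randomisation makes the two arms comparable only if membership of the analysed groups does not depend on what happens afterwards. Here it does, and in one arm only. A control patient cannot fall below 50% adherence to a drug that was never given.

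The selection is also plausibly tied to the outcome. Section 2.4 defines the endpoint as follows: "The primary outcome of the trial is the incidence of gastrointestinal symptoms at 1 month postoperatively in gastric cancer patients". The seven symptoms counted include nausea, vomiting, dysphagia and abdominal distension. A patient with these may be unable to keep up three capsules three times a day with food. Dropping such patients removes outcome events from PERT and none from control.

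At stake is whether the primary result can be read as a randomised comparison. A drug with no effect could look beneficial, and the actual type I error could lie above the planned 5%.

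**Working it through.** **The plan's own figure.** Section 2.6 gives 50% (control), 30% (PERT), two-sided 5%, power 80% and 10% dropout. With unpooled variance:

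n = (1.960 + 0.842)² × (0.50×0.50 + 0.30×0.70) / 0.20² = 7.849 × 0.46 / 0.04 = 90.3, so 91 per arm.

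91 / 0.9 = 101.1, so 102 per arm and 204 in total. The stated sample size reproduces. The problem lies in the analysis population, not in the sample size.

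**Inputs for the bias.**

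- From the article: 50% control rate, 102 per arm, 10% dropout. This leaves 102 × 0.9 = 91.8, taken as 92 evaluable per arm.
- Assumed, because the article gives neither: f, the fraction of PERT patients excluded, and q, the symptom rate among them.

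**Formula.** If the true rate is 50% in both arms, the rate among the retained PERT patients is

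r = (0.50 − f × q) / (1 − f),

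and the spurious difference is 0.50 − r. Example with f = 20%, q = 80%: r = (0.50 − 0.16) / 0.80 = 0.425, which is 7.5 points towards PERT.

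**Type I error.** This is the exact rejection probability of the two-sided Pearson chi-square test at 5%, summed over all outcomes, with 92 controls at 50% and 92 × (1 − f) PERT patients at r (83, 74 and 69 after rounding). With no exclusion it is 4.6%.

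| Symptom rate q among the excluded | 10% excluded | 20% excluded | 25% excluded |
|---|---|---|---|
| 80% | 3.3 points towards PERT; 7.3% | 7.5 towards; 16.2% | 10.0 towards; 24.5% |
| 60% | 1.1 towards; 5.3% | 2.5 towards; 6.2% | 3.3 towards; 7.1% |
| 50% | none; about 5% | none; about 5% | none; about 5% |
| 30% | 2.2 points against PERT; 6.1% | 5.0 against; 9.9% | 6.7 against; 13.5% |

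Where q is above 50%, the excess rejections favour PERT. Where q is below 50%, they go against it.

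**Sensitivity to the base.** Section 2.6 does not say whether the 10% dropout allowance is meant to cover adherence exclusions as well. With all 102 per arm as the base and a normal approximation, q = 80% gives 7.5% at f = 10% and 17.2% at f = 20%, so the picture is the same.

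**If the drug works as planned** (true PERT rate 30%, true difference 20 points, f = 20%):

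- q = 50%: r = (0.30 − 0.10) / 0.80 = 25.0%, an apparent difference of 25.0 points.
- q = 20%: r = (0.30 − 0.04) / 0.80 = 32.5%, an apparent difference of 17.5 points.

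The effect estimate is therefore distorted under the alternative as well.

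**The case against.** The strongest objection concerns direction. A reader might infer that the rule necessarily favours PERT. The article does not support that: it gives no reasons for non-adherence and no symptom rate among non-adherers. Patients who feel well may also skip capsules, and dropping them biases against PERT, as the 30% row shows. This objection stands. Bias towards PERT is the more plausible and more worrying case, but it is not established.

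A reader might likewise infer that the type I error does exceed 5%. That is conditional on f and q. At 60% symptomatic and 10% excluded it is 5.3%, and the figures of 16.2% and 24.5% need both heavy non-adherence and strong selection.

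A third tempting reading is that the two sentences of section 2.7 cannot both be carried out. They can: an analyst may form the full analysis set and then apply the exclusion. The result is simply not an intention-to-treat analysis, whatever it is called.

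Finally, a condensed article may have shortened a per-protocol definition in the full protocol into this one sentence. That is possible. As printed, however, the rule is unqualified and sits directly after the intention-to-treat claim, so it needs correcting either way.

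**Conclusion.** The point holds as a defect of the stated analysis population. Section 2.7 applies a one-sided exclusion after randomisation, contrary to the principle it invokes. That conclusion needs no assumption about f or q.

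The resulting bias is possible and plausibly towards PERT, but neither its size nor its sign can be fixed from the article. Over the assumed ranges (10% to 25% of PERT excluded, 30% to 80% of them symptomatic, true null), it runs from 10.0 points towards PERT to 6.7 points against. Type I error runs from about 5% to 24.5%. There is no bias only if those excluded have the same symptom rate as the rest of their arm, and nothing in the article gives reason to expect that. The correction should be made before the arms are compared.

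**What to change.** 1. In section 2.7, state that the primary analysis includes all randomised patients in the arm assigned, regardless of adherence.
2. Move the 50% rule to a per-protocol set, labelled as supportive only.
3. Reword the one-dose condition in the full analysis set. Read literally, no control patient can meet it, and it conflicts with item 1.
4. Reconcile exclusion criterion 8 in Table 1 with item 1, so that interrupting the drug does not remove PERT patients from the primary analysis set. Without items 3 and 4, deleting the adherence sentence alone would leave the set asymmetric.
5. Because section 2.5 stops follow-up at withdrawal, the analysis plan should say how patients without a 1-month outcome are handled in the all-randomised set.

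Enrolment began on 6 June 2025 (section 2.3), so the amendment should be dated and made before outcomes are compared by arm.

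The cost is wording, plus possible dilution of the effect. If 10% of PERT patients gain nothing, the expected PERT rate is 0.9 × 30% + 0.1 × 50% = 32%. Power against 50% is then about 70% with 92 per arm and about 76% with all 102. The sponsor should accept that loss knowingly or consider whether 204 is still enough.
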